#### Type of study

3.1.3

A randomized and blind controlled clinical trial will be conducted.

#### Participants

3.1.4

Forty-eight teeth of healthy 6 to 12-year-old children of both genders, without distinction of race or ethnicity, will be selected at the clinic of the dentistry course of Nove de Julho University (São Paulo, Brazil).

#### Inclusion criteria

3.1.5

1.Healthy children, without systemic alterations;2.Collaborative children;3.Present 1 permanent molar with the code 6 on MIH severity scoring system (MIH-SSS), active and acute caries lesion in dentin, not exceeding 2/3 and involving only the occlusal, with direct vision and access, without clinical and radiographic signs and symptoms of pulp involvement.

#### Exclusion criteria

3.1.6

1.Child with systemic impairment;2.Non-cooperative behavior;3.Carious lesion of Class II, III, IV, or V type of Black;4.Clinically: carious lesion involving enamel, deficient restorations, small carious lesions in dentin (without access to hand excavators), occult caries lesions, clinical sign and/or symptom of pulp involvement, clinical impossibility of restoration;5.Radiographically: evidence of pulpal involvement, carious lesion extending beyond two-thirds of the dentin.

#### Interventions

3.1.7

##### Group 1

3.1.7.1

1.Initial interproximal radiography;2.Relative insulation (lip retractor, cotton roller, and saliva sucker);3.Taking the VAS scale for pain as responded by the volunteer;4.Microbiological outlet with an otoscopic curette to standardize the volume of carious tissue;5.Application—(PapacarieMblue), leave action for 20 seconds and remove the softened carious tissue just around the sidewalls of the cavity with blunt dentin spoons. Wait another 3 minutes to act on the blue dye present in the gel composition;6.Radiate with the low power laser (single point), following the parameters described in item 3.1.10;7.Clean with cotton ball and water;8.Second microbiological outlet with curette of remaining dentin tissue;9.Clinical evaluation by inspection of remaining dentin texture with rounded probe exploratory probe;10.Clean with cotton ball and water again;11.Sealing the cavity with glass ionomer cement (Riva Self Cure/HV - SDI);12.Taking VAS for Pain Responded by Volunteer;13.Preservation;14.Radiographic control 6 and 12 months.

##### Group 2

3.1.7.2

1.Initial interproximal radiography;2.Relative insulation (lip retractor, cotton roller, and saliva sucker);3.Microbiological outlet with an otoscopic curette to standardize the volume of carious tissue;4.Removal of the softened dentin dentine around the lateral walls of the cavity with sharp dentine curettes # 17;5.Second microbiological outlet with dentin curette;6.Clinical evaluation by inspecting the texture of the remaining dentin with exploratory catheter;7.Clean with cotton ball and water;8.Sealing the cavity with glass ionomer cement (Riva Self Cure/HV - SDI);9.Preservation;10.Radiographic control 6 and 12 months.

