#### Microbiological evaluation

3.1.13

Prior to the removal, the soft dentine of each selected tooth will be collected. The removed tissue will be standardized using a No. 2 Meyhoefer curette and will be deposited in a test tube containing 3.8 mL of Transport Medium-Phosphate Buffered Saline (PBS, Labcenter, São Paulo). The biological material will be deposited in the transport flask containing glass beads by shaking the tube at maximum speed in a Vortex apparatus for homogenization of the biological material for 30 seconds. After stoving at 37°C for 30 minutes to liquefy the gelatin from the medium, the dental biofilm will be dispersed into the transport flask containing glass beads by shaking the tube shaker at full speed for 30 seconds.

Subsequently, biological material will be serially diluted in the order of 10^1^ to 10^6^ in peptone water and inoculated into culture media in Petri dishes. Aliquots of dilutions 10^4^, 10^5^, and 10^6^ will be seeded on the surface of Brucella Agar (Difco, Kansas City, USA) plus sheep defibrinated blood (50 mL/L), hemin (Inlab, São Paulo, Brazil) (5 mg/mL), and menadione (Inlab) (10 mg/mL) for the determination of the total viable microorganisms. Aliquots of dilutions 10^3^ and 10^4^ will be seeded in MitisSalivarius agar medium (Difco) to determine the total number of streptococci (S). Biofilm aliquots without dilution and at dilutions 10^1^ and 10^2^ will be seeded in MitisSalivarius Agar medium plus debacitracin to determine the streptococci mutans (SM) population.^[39]^ 100 μL aliquots of each dilution will be seeded on the agar surface and spread with the aid of a Drigalski loop.

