In order to verify the presence of lactobacilli (LB), aliquots (100 μL) without dilution and in the dilution 10^2^ will be inoculated in depth (Agarplate Rogosa SL (Difco).^[39]^ Brucella Agar plates will be incubated in anaerobic chamber (PLAS by LABS, LANSING, MICH., USA) at 37°C for 7 days. The plates of MitisSalivarius Agar and MitisSalivarius Bacitracin will be incubated in 10% CO2 (ShelLab CO2 greenhouse, mod. 2123, Oregon) at 37°C for 48 hours. Plates containing Rogosa Agar will be incubated in 10% CO2 at 37°C for 72 hours.^[39]^ After the incubation, the characteristic colonies will be counted in each plate, observed using a stereoscopic microscope with 10-fold increase, in the dilution that presented between 30 and 300 colonies per plate. All procedures will be performed in duplicate and the average counts will be calculated.

The results will be presented in CFU of SM and LB and in percentage of streptococci (% S/TM), streptococci mutans (% SM/TM), and lactobacilli (% LB/TM) in relation to total viable microorganisms. For SM, the proportion of total streptococci (% SM/S)^[15]^ will also be calculated. Immediately after removal of the carious tissue, the remaining dentin will be collected using the Meyhoefer auricular No. 17 curette and the same procedures described above will be adopted.

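### As listed, the second bacterial sample follows a cotton-and-water clean in Group 1 but precedes it in Group 2, so the between-arm CFU comparison is confounded with cleaning

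*Protocol article*

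**What the plan says.** Section 3.1.7 of the protocol article lists the steps for each arm. For Group 1 it has "7.Clean with cotton ball and water;8.Second microbiological outlet with curette of remaining dentin tissue", and after the probe examination a further clean, "10.Clean with cotton ball and water again". For Group 2 the order is "5.Second microbiological outlet with dentin curette;6.Clinical evaluation by inspecting the texture of the remaining dentin with exploratory catheter;7.Clean with cotton ball and water". Group 2 has no other clean.

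Section 3.1.13 describes the sampling without distinguishing the arms. At baseline, "The removed tissue will be standardized using a No. 2 Meyhoefer curette". Afterwards, "Immediately after removal of the carious tissue, the remaining dentin will be collected using the Meyhoefer auricular No. 17 curette". No clean is mentioned there.

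Section 3.1.9 gives another sequence for Group 1: gel, removal, gel again, laser, then selective removal with a curette, cleaning and restoration. It does not say where the second sample falls.

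CFU is the variable behind the sample size (3.1.8), and decontamination is one of the two effects claimed in H1 (3.1.2). The stated primary outcome is dentin sensitivity on the VAS (3.1.12).

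**The concern.** If section 3.1.7 is followed, every second sample in Group 1 comes from a cavity that has just been wiped with wet cotton, and no second sample in Group 2 does. Wiping can plausibly carry away loose debris and bacteria. A lower Group 1 count could then come from the clean, from the aPDT, or from both. Because the clean is tied to arm in every tooth, no later analysis can separate the two. Adjusting for baseline does not help, since the clean happens between the two samples.

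The sampling time itself is also unsettled. If sites follow section 3.1.13 rather than 3.1.7, Group 1 could be sampled before the laser is used, and the count would then say nothing about the photodynamic step.

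At stake is the microbiological comparison between arms.

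**Working it through.** **1. Position of the second sample in section 3.1.7**

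| | Group 1 | Group 2 |
|---|---|---|
| Tissue removal | step 5 | step 4 |
| Laser | step 6 | none |
| Clean before second sample | step 7 | none |
| Second sample | step 8 | step 5 |
| Clean after second sample | step 10 | step 7 |

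The row for the clean before sampling differs between arms for every tooth.

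**2. Section 3.1.13 set against the two Group 1 sequences**

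- With the 3.1.7 list, sampling straight after removal (step 5) would fall before the laser (step 6) and before the clean (step 7).
- With the 3.1.9 sequence, the selective removal comes after the laser, so sampling straight after it would fall after irradiation and before the clean. That is the same position relative to the clean as in Group 2. Section 3.1.9 also mentions a removal before the second gel application, so even there the reference point needs to be named.
- For Group 2, 3.1.13 and 3.1.7 agree.

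The three sections therefore allow at least three sampling points in Group 1: before the laser, after the laser but before the clean, and after both.

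**3. Possible size of the cleaning effect**

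The plan's minimum of 16 teeth per group (3.1.8) cannot be reproduced, because the CFU difference and SD are not in the readable text. Back-solving with 1.96 + 0.84 = 2.80 gives:

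- paired formula: 2.80/√16 = 0.70 SD
- two independent groups of 16: 2.80 × √(2/16) = 0.99 SD
- two independent groups of 24, as planned: 2.80 × √(2/24) = 0.81 SD

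The documents say nothing about how much a clean removes, so what follows is an illustration. Assume a share r of recoverable CFU is removed by the clean, analysis on the log10 scale with standard deviation SD, no treatment effect, 24 independent teeth per group, and a two-sided 5% test. Then

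- shift b = −log10(1 − r)/SD, in SD units
- SE = √(2/24) = 0.289
- chance of a significant result = Φ(b/SE − 1.96) + Φ(−b/SE − 1.96)

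Example with r = 50% and SD = 1.0: b = 0.301, b/SE = 1.04, and Φ(−0.92) + Φ(−3.00) ≈ 0.18.

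| r (assumed) | log10 shift | SD 0.5 | SD 1.0 | SD 1.5 |
|---|---|---|---|---|
| 10% | 0.05 | 6% | 5% | 5% |
| 25% | 0.12 | 14% | 7% | 6% |
| 50% | 0.30 | 55% | 18% | 11% |
| 75% | 0.60 | 99% | 55% | 28% |

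The nominal rate is 5%. The range runs from negligible to serious.

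**4. The curette change**

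Let the No. 17 collect k times the volume of the No. 2, in both arms. The before-after change on the log10 scale is then shifted by log10(k) in each arm: 0.30 for k = 2 and 0.48 for k = 3 (both ratios assumed). In the between-arm difference of changes, log10(k) − log10(k) = 0. The change therefore distorts the before-after result within each arm and gives neither arm an advantage.

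**The case against.** Four arguments deserve an answer.

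- **Gel carry-over.** Only Group 1 receives a gel, and the Introduction describes its components as disinfecting and bactericidal. A clean before sampling may be meant to limit carry-over of gel and dye into the culture. That is a fair reason to clean Group 1. It is also a reason to clean the control at the same point.
- **Percentage outcomes.** Section 3.1.13 also reports streptococci, mutans streptococci and lactobacilli as percentages of total microorganisms. These are little affected if the clean lowers all organisms in proportion. The absolute counts of mutans streptococci and lactobacilli, which are also reported, have no such protection.
- **The sample is curetted dentin.** Loose surface material may contribute little to a curetted sample, so the effect could be small. This stands, and it is why no size is claimed.
- **Other differences between arms.** Gel and excavation instrument differ too, so matching the clean would not isolate the laser. True, but those belong to the treatments being compared. The clean before sampling is a difference in how the outcome is measured.

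A reader might go further and infer that the CFU result will favour aPDT whatever the treatment does. The documents do not support that: the cleaning effect is unknown, and the sampling order is itself contradictory. A reader might also count the curette change as bias towards aPDT. Section 3.1.13 applies it to both arms alike, so it is not. Nor does the number 17 on Group 2's excavation curettes show that they are the same instrument as the No. 17 used for sampling.

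**Conclusion.** The point holds in a limited form. Under section 3.1.7 the between-arm CFU comparison is confounded with cleaning, probably towards lower counts with aPDT. The amount cannot be derived from the documents. With 25% to 50% of CFU removed and a log10 SD of 0.5 to 1.5, all assumed, the chance of a spurious significant difference is 6% to 55% against a nominal 5%. Sections 3.1.7, 3.1.9 and 3.1.13 also conflict on the order of steps, and one reading samples Group 1 before irradiation.

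This concerns the sizing variable and the decontamination part of H1. The VAS primary outcome is not touched. It should be settled before the first tooth is sampled, because the analysis cannot repair it afterwards.

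The change from a No. 2 to a No. 17 curette is a separate and smaller matter. It mixes sample volume into the before-after change in both arms without favouring either.

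**What to change.** - Reconcile sections 3.1.7, 3.1.9 and 3.1.13 so that they give one sequence for Group 1. Which treatment sequence applies is for the investigators to settle.
- State one sampling rule for both arms in 3.1.13, and bring both step lists in 3.1.7 into line with it. The second sample is taken once the allocated intervention is complete (in Group 1, after irradiation) and at the same point relative to the cotton-and-water clean in both groups.
- Use the same size of sampling curette at baseline and at the second sample.

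The cost is a reordering of the sampling and cleaning steps in one list, one rewritten sentence in 3.1.13, and a second sampling curette of the same size for each tooth. Neither the sample size nor the allocation changes.

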#### Experimental groups

3.1.9

Forty-eight teeth of healthy 6 to 12-year-old children of both genders, without distinction of race or ethnicity in the clinic of the dentistry course of Nove de Julho University (São Paulo, Brazil) will be select.

The participants will be allocated in the experimental groups as follows:

Group 1—PDT + atraumatic restaurative treatment (ART) (n = 24): for the PDT the PapacarieMblue (Fórmula e Ação) will be used. It will be left for 5 minutes in the cavity. The carious tissue will be removed and the application of the PapacarieMblue will be repeated. The tissue will then be irradiated in a single spot with a red laser, of wavelength of 660 nm, for 60 seconds, with the energy of 6J. These parameters were also applied in the vestibular root of the teeth, to try and prevent sensitivity. Laser parameters can be found in item 3.1.10. Selective removal of carious tissue will be made with a curette, followed by cavity cleaning and restoration with Riva Self Cure/HV – SDI.

Group 2—Atraumatic restaurative treatment (ART) (n = 24): Removal of infected dentin with a curette only, followed by cavity cleaning and restoration with Riva Self Cure/HV – SDI.

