#### Statistical analysis

3.1.17

Data will be analyzed statistically using different tests, considering the level of significance of 5%. The data obtained will be submitted to descriptive statistical analysis to evaluate the association of categorical variables. Chi-square test and Fisher exact test will be applied, and to analyze the correlation between the continuous variables, Pearson correlation test will be applied. For the analysis of dentin density in the scanned radiographic images and the microbiological results for colony-forming units, ANOVA and Kruskal–Wallis will be applied.

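### The second bacterial sample follows a cotton-and-water clean in Group 1 but precedes any clean in Group 2, and sections 3.1.7, 3.1.9 and 3.1.13 conflict on when it is taken

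*Protocol article*

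**What the plan says.** Three places in the protocol article bear on the timing of the post-treatment bacterial sample.

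- **Section 3.1.7, Interventions.** In Group 1, gel and excavation are step 5 and the laser is step 6. Steps 7 and 8 are "Clean with cotton ball and water;8.Second microbiological outlet with curette of remaining dentin tissue". After a texture check (step 9) comes a further clean at step 10: "Clean with cotton ball and water again". In Group 2, excavation is step 4, and steps 5 to 7 are "Second microbiological outlet with dentin curette;6.Clinical evaluation by inspecting the texture of the remaining dentin with exploratory catheter;7.Clean with cotton ball and water".
- **Section 3.1.13, Microbiological evaluation.** One rule covers the second sample, with no distinction by arm: "Immediately after removal of the carious tissue, the remaining dentin will be collected".
- **Section 3.1.9, Experimental groups.** For Group 2: "Removal of infected dentin with a curette only, followed by cavity cleaning and restoration". For Group 1, selective removal with a curette is placed after irradiation, and cleaning and restoration come after that. This section does not mention the sample.

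Section 3.1.17 states that for "the microbiological results for colony-forming units, ANOVA and Kruskal–Wallis will be applied". Section 3.1.8 sizes the trial on CFU, with a minimum of 16 teeth per group. Section 3.1.9 plans 24 per group.

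**The concern.** Both arms are cleaned before the cavity is sealed, but in the 3.1.7 lists the second sample falls on opposite sides of that clean. If wiping and rinsing removes organisms that the curette would otherwise recover, Group 1 shows lower post-treatment CFU for a reason unrelated to light or photosensitiser. The step differs completely by arm, so no between-arm analysis of raw CFU can separate it from the treatment. Adjusting for the first sample does not help, because the difference arises after that sample is taken.

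What is at stake is the CFU comparison: decontamination is part of H1 in section 3.1.2, and CFU is the variable used to size the trial. The other sections do not settle the matter, because they describe a different order for Group 1.

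**Working it through.** **1. Order of steps.**

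| Source | Group 1 | Group 2 |
|---|---|---|
| 3.1.7 | excavate, wait, laser, clean, **sample**, texture check, clean | excavate, **sample**, texture check, clean |
| 3.1.13 | **sample** immediately after removal | **sample** immediately after removal |
| 3.1.9 | laser, selective removal, clean, restore (sample not placed) | removal, clean, restore (sample not placed) |

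Group 2 is consistent across all three. Group 1 is not. In 3.1.7 a 3-minute wait, the laser and a clean stand between excavation and sampling. Sections 3.1.9 and 3.1.13 read together put the sample before the clean in both arms. Applying the 3.1.13 rule literally to the 3.1.7 order would put the Group 1 sample before the laser, which cannot be intended for a post-treatment sample.

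**2. The plan's own figure.** The minimum of 16 per group cannot be reproduced forward: the text gives no CFU difference or SD, and the formula is in a figure not shown. Solving backward with (1.96 + 0.84)² = 7.84:

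- paired: d = √(7.84/16) = 0.70 SD;
- two independent groups: d = √(2 × 7.84/16) = 0.99 SD;
- at the planned 24 per group, independent: √(2 × 7.84/24) = 0.81 SD detectable with 80% power.

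Nothing here shows that 16 is wrong.

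**3. How large the artefact could be.** The documents do not say what share *f* of recoverable CFU the clean removes, nor the SD of log10 CFU. Both are assumptions. Take aPDT to have no effect.

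- Artefact in log10 CFU: a = −log10(1 − f).
- Noncentrality: (a/SD) × √(24/2).
- Rejection probability: two-sided 5% two-sample t test, 46 df, critical value 2.013.

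Example: f = 0.5 gives a = 0.301; with SD 1.0 the noncentrality is 0.301 × 3.464 = 1.04.

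| Share removed | Artefact (log10) | Rejection, SD 1.0 | Rejection, SD 1.5 |
|---|---|---|---|
| 10% | 0.05 | 5.3% | 5.1% |
| 20% | 0.10 | 6.2% | 5.6% |
| 30% | 0.15 | 8.2% | 6.4% |
| 50% | 0.30 | 17.5% | 10.5% |
| 70% | 0.52 | 42.6% | 21.9% |
| 90% | 1.00 | 92.4% | 61.8% |

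The nominal rate is 5%, so the artefact ranges from negligible to dominant over this span.

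**4. Which outcomes it reaches.** Section 3.1.13 also reports percentages: streptococci, mutans streptococci and lactobacilli over total viable organisms, and mutans over total streptococci. A clean that removes all organisms in the same proportion cancels in these ratios, so they are less exposed than raw CFU. The VAS measurement in 3.1.12 does not depend on the sample.

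**The case against.** The strongest reply is that the asymmetry appears in one list only. Sections 3.1.9 and 3.1.13 together describe sampling before cleaning in both arms, so the article may reflect a drafting slip and not a chosen design. That stands, and it is why the point is a conflict to be reconciled. It does not remove the risk, because the numbered list is what an operator would most naturally follow.

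Second, the effect may be small. The sample is dentin taken with a curette, not a surface swab, and a wipe with water may hardly change what is recovered. This also stands: at 10–30% removal the error rate barely moves. A reader might infer from the step order that the trial is bound to favour aPDT, or that a CFU benefit would be produced by the wash. The documents do not support that. They give no figure for the clean, so a bias towards aPDT is the expected direction and no more.

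Third, a reader might conclude that the trial's main result is compromised. It is not. The primary outcome is VAS sensitivity, and H0 in section 3.1.2 itself grants that bacteria are reduced, so H1 and H0 as worded differ on sensitivity.

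Fourth, the Group 1 clean may serve to remove gel and dye before sampling, and the arms also differ in gel, waiting time and instruments. The document does not state the purpose of the clean. The gel belongs to the package under test. The timing of a clean that both arms receive is an avoidable measurement difference, and matching it does not require dropping it from Group 1.

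**Conclusion.** The point holds as an internal conflict with a possible bias in a secondary but important outcome. Followed as printed, the 3.1.7 lists confound the cotton-and-water clean with arm for post-treatment raw CFU, and the remaining text contradicts the Group 1 order. The size cannot be established from the documents. The rejection rates above rest on assumed removal shares and SDs, 24 independent teeth per arm, a t test on log10 CFU and no true aPDT effect. The VAS primary outcome is untouched, and the percentage outcomes are affected less. The point deserves correction because the remedy is cheap and a tooth's post-treatment sample cannot be retaken, not because the bias has been shown to be large.

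**What to change.** Reconcile sections 3.1.7, 3.1.9 and 3.1.13 so that the second sample is taken at the same point relative to the cotton-and-water clean in both arms. Either option works: before the clean in both, or after the same clean in both.

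State that single rule in 3.1.13, replacing its present wording if the after-clean option is chosen, and say explicitly where the Group 1 sample stands relative to irradiation. Then make the lists in 3.1.7 and the summaries in 3.1.9 match. In choosing, the sponsor should consider whether gel left in the cavity could carry over into the Group 1 sample, since the Introduction attributes antibacterial action to its components.

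The cost is one reordered line and at most one extra cotton ball per tooth. No change to sample size, visits or staff follows. If teeth have already been sampled, report the order actually used in each arm and limit the interpretation of raw CFU accordingly.
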